**10. DATE OF REVISION OF THE TEXT**

<http://emc.medicines.org.uk/emc/assets/c/html/DisplayDoc.asp?DocumentID=7855>

SUPPORTING INFORMATION

Patient Information Leaflet:
[Zoladex 3.6mg Implant](http://emc.medicines.org.uk/emc/assets/c/html/DisplayDoc.asp?DocumentID=10755)

Alternative format PIL:
[Zoladex 3.6mg Implant (new window)](http://xpil.medicines.org.uk/ViewPil.aspx?docid=10755)

Medicine Guide:
[Zoladex (new window)](http://medguides.medicines.org.uk/document.aspx?name=Zoladex)

APPENDIX 2: Monitoring Plan

1. Trial oversight committees:

|  | **Y** | **N** | **N/A** |
| --- | --- | --- | --- |
| Trial management group |  | X |  |
| Independent data monitoring committee |  | X |  |
| Trial Steering committee |  | X |  |
| Other/comments: | | | |

2. Central monitoring:

|  | **Y** | **N** | **N/A** |
| --- | --- | --- | --- |
| Data collected and validated via central coordinating centre (‘good housekeeping’) |  | X |  |
| Trial data recorded on database with inbuilt data checks (eg value ranges etc) |  | X |  |
| Randomisation done via central coordinating centre (verify eligibility) |  | X |  |
| Central pharmacovigilance reporting procedure | X |  |  |
| Investigator training/Investigator meetings |  |  | X  (single site) |
| Other/comments: | | | |

3. On-site monitoring:

|  | **Y** | **N** | **N/A** |
| --- | --- | --- | --- |
| Investigator Site File | X |  |  |
| SDV informed consent | X |  |  |
| SDV of critical data (eg endpoint data, dose adjustments, concomitant medication) | X |  |  |
| SDV of safety data (AEs, SAE, SUSARs) and timeliness of reporting | X |  |  |
| SDV patient eligibility | X |  |  |
| Storage and security of trial data | X |  |  |
| Pharmacy documentation |  | X |  |
| Study drug accountability |  | X |  |
| Study drug storage |  | X |  |
| Other/comments:  IMP used within licence therefore pharmacy will not be monitored unless requested by CI/Co-Sponsor | | | |

**4. Expected frequency of on-site monitoring of lead site (or local site) and document the plan for monitoring of external sites if applicable:**

(This will be based on the risk assessment and the number and type of central monitoring strategies for a particular trial).

| This is a single site study.  Study start-up visit prior to recruitment.  1-2 visits during patient recruitment to review ISF, SDV trial data, check 100% consent forms.  Study closure visit after patient recruitment and analysis of results. |
| --- |

APPENDIX 3: Risk Assessment

**RISK ASSESSMENT TOOL FOR MONITORING**

| **MONITORING CRITERIA*** | **Y** | **N** | **N/A** |
| --- | --- | --- | --- |
| Is the research sponsored or co-sponsored by The University of Edinburgh and/or NHS Lothian? | X |  |  |
| IMP trial?   - IMP used in novel setting or indication not listed in SmPC - IMP to be used within strict settings? (e.g. storage temperatures, short shelf life etc). | X | X  X |  |
| Hazards of assessment methods eg x-ray, biopsy etc |  | X |  |
| Risk of SAE/SUSARs (greater than that expected as part of routine care)? |  | X |  |
| Research involving children?  Research involving other vulnerable patient group? |  | X  X |  |
| Complex protocol? |  | X |  |
| Large intake? |  | X |  |
| Randomised or blinded trial? | X |  |  |
| Potential for high subject drop-out/withdrawal rate? |  | X |  |

*Studies will be monitored if they meet one or more of the above criteria. Studies that meet multiple criteria will be monitored in more depth and more frequently than studies that meet only one criterion.

APPENDIX 4: Study plan

Pilot Group A - GnRH agonist Only (Goserelin 3.6mgs) (n=15)

| **Day of Treatment** | **Visits/Interventions** | **U&Es**  **FBC**  **LFTs** | **Concomitant**  **Meds** | **Adverse Events** | **E2, P, FSH, LH** |
| --- | --- | --- | --- | --- | --- |
| Screening | Informed Consent  Inclusion & Exclusion Criteria  Medical & Menstrual History  Physical Exam & Vital Signs  Height & Weight  Urinalysis & Pregnancy Test  Ultrasound  Doppler (if required) | **X** | **X** |  |  |
| Within  28 days  of Day 1 | **Visit 1**  1.5T MRI, Ultrasound & Doppler (if required)  Cannulation & Gadolinium |  | **X** | **X** |  |
|  | **GnRH agonist**  (Goserelin 3.6mg s/c)  **clinically indicated and requested by clinician** |  |  |  |  |
| **1**  (Days 1 to 5 of cycle) | GnRH agonist **Dose 1**  (Goserelin 3.6mg s/c) |  | **X** | **X** |  |
| 28 days from Dose 1 +/- 3 days | GnRH agonist **Dose 2**  (Goserelin 3.6mg s/c) | **X** | **X** | **X** |  |
| 28 days from Dose 2 +/- 3 days | GnRH agonist **Dose 3**  (Goserelin 3.6mg s/c)  This dose may not be  clinically requested |  | **X** | **X** |  |
| Up to 10 days  Prior to  Hysterectomy | **Visit 2**  1.5T MRI, Ultrasound & Doppler  Cannulation & Gadolinium |  | **X** | **X** |  |
| 21 – 28 days from  GnRH agonist Dose 2 or 3 | **Visit 3**  Hysterectomy  7T MRI of Uterus  Histo-morphology | **X** | **X** | **X** | **X** |

(Version 2 13th October 2009)

**The following are NOT required for Pilot Groups -**

**Urine Sample (5mls) collected twice weekly from Visit 1**

**Daily Menstrual Recording Chart from Visit 1**

**Pilot Group B – No treatment (n=1**5)

| **Day of Treatment** | **Visits/Interventions** | **U&Es**  **FBC**  **LFTs** | **Concomitant**  **Meds** | **Adverse Events** | **E2, P, FSH, LH** |
| --- | --- | --- | --- | --- | --- |
| Screening | Informed Consent  Inclusion & Exclusion Criteria  Medical & Menstrual History  Physical Exam & Vital Signs  Height & Weight  Urinalysis & Pregnancy Test  Ultrasound  Doppler (if required) | **X** | **X** |  |  |
|  | **No treatment requested by clinician** |  |  |  |  |
| **Up to 10 days**  **Prior to**  **Hysterectomy** | **Visit 1**  1.5T MRI, Ultrasound & Doppler (if required)  Cannulation & Gadolinium |  | **X** | **X** |  |
|  | **Visit 2**  Hysterectomy  7T MRI of Uterus  Histo-morphology | **X** | **X** | **X** | **X** |

(Version 2 13th October 2009)

**The following are NOT required for Pilot Groups -**

**Urine Sample (5mls) collected twice weekly from Visit 1**

**Daily Menstrual Recording Chart from Visit 1**

**Pilot Group C – No treatment 2 Novel MRI scans (n=5)**

| **Day of Treatment** | **Visits/Interventions** | **U&Es**  **FBC**  **LFTs** | **Concomitant**  **Meds** | **Adverse Events** | **E2, P, FSH, LH** |
| --- | --- | --- | --- | --- | --- |
| Screening | Informed Consent  Inclusion & Exclusion Criteria  Medical & Menstrual History  Physical Exam & Vital Signs  Height & Weight  Urinalysis & Pregnancy Test  Ultrasound  Doppler (if required) | **X** | **X** |  |  |
|  | **No treatment requested by clinician** |  |  |  |  |
| **Up to 10 days**  **Prior to**  **Hysterectomy** | **Visit 1**  1.5T MRI, 3T MRI, Ultrasound & Doppler (if required)  Cannulation & Gadolinium |  | **X** | **X** |  |
|  | **Visit 2**  Hysterectomy  7T MRI of Uterus  Histo-morphology | **X** | **X** | **X** | **X** |

(Version 1 13th October 2009)

**The following are NOT required for Pilot Groups -**

**Urine Sample (5mls) collected twice weekly from Visit 1**

**Daily Menstrual Recording Chart from Visit 1**

**Group 1 GnRH agonist Only (Goserelin 3.6mgs) (n=10)**

| **Day of Treatment** | **Visits/Interventions** | **U&Es**  **FBC**  **LFTs** | **E2, P4,**  **LH, FSH**  **Time Points** | **Concomitant**  **Meds** | **Adverse Events** |
| --- | --- | --- | --- | --- | --- |
| Screening | Informed Consent  Inclusion & Exclusion Criteria  Medical & Menstrual History  Physical Exam & Vital Signs  Height & Weight  Urinalysis & Pregnancy Test  Ultrasound  Doppler (if required**)** | **X** |  | **X** |  |
| Within  28days  of Day 1 | **Visit 1**  1.5T MRI, Ultrasound & Doppler (if required)  Cannulation & Gadolinium |  | **1** | **X** | **X** |
|  | **Randomisation** |  |  |  |  |
| **1**  (Days 1 to 5 of cycle) | GnRH agonist **Dose 1**  (Goserelin 3.6mg s/c) |  | **2** | **X** | **X** |
| 4+/- 1 |  |  | **3** | **X** | **X** |
| 7+/- 1 |  |  | **4** | **X** | **X** |
| 11+/- 1 |  |  | **5** | **X** | **X** |
| 14+/- 3 | **Visit 2**  1.5T MRI, Ultrasound & Doppler |  | **6** | **X** | **X** |
| 28 +/- 3 days from Dose 1 | **Visit 3**  GnRH agonist **Dose 2**  (Goserelin 3.6mg s/c)  MRI, Ultrasound & Doppler  Cannulation & Gadolinium | **X** | **7** | **X** | **X** |
| 28 +/- 3 days from Dose 2 | GnRH agonist **Dose 3**  (Goserelin 3.6mg s/c) |  | **8** | **X** | **X** |
| Within 10 days of TAH | **Visit 4**  1.5T MRI, Ultrasound & Doppler  Cannulation & Gadolinium |  | **9** | **X** | **X** |
| 21-28 days from Dose 3 | **Visit 5**  Hysterectomy  7T MRI of Uterus  Histo-morphology | **X** | **10** | **X** | **X** |

(Version 2 13th October 2009)

**In Addition -**

**Urine Sample (5mls) collected twice weekly from Visit 1**

**Daily Menstrual Recording Chart from Visit 1**

**Group 2 GnRH antagonist (Cetrorelix 3mgs) and GnRH agonist (Goserelin** 3.6mgs)(n=10)

| **Day of Treatment** | **Visits/Interventions** | **U&Es**  **FBC**  **LFTs** | **E2, P4,**  **LH, FSH**  **Time Points** | **Concomitant**  **Meds** | **Adverse Events** |
| --- | --- | --- | --- | --- | --- |
| Screening | Informed Consent  Inclusion & Exclusion Criteria  Medical & Menstrual History  Physical Exam & Vital Signs  Height & Weight  Urinalysis & Pregnancy Test  Ultrasound  Doppler (if required) | **X** |  | **X** |  |
| Within  28 days  of Day 1 | **Visit 1**  1.5T MRI, Ultrasound & Doppler (if required**)**  Cannulation & Gadolinium |  | **1** | **X** | **X** |
|  | **Randomisation** |  |  |  |  |
| 1  (Days 1 to 5 of cycle) | GnRH antagonist **Dose 1**  (3 mg Cetrorelix s/c) |  | **2** | **X** | **X** |
| 4+/- 1 day | GnRH antagonist **Dose 2**  (3 mg Cetrorelix s/c) |  | **3** | **X** | **X** |
| 7+/- 1 day | GnRH antagonist **Dose 3**  (3 mg Cetrorelix s/c)  GnRH agonist **Dose 1**  (Goserelin 3.6mg s/c) |  | **4** | **X** | **X** |
| 11+/- 1 day |  |  | **5** | **X** | **X** |
| 14+/- 3 days | **Visit 2**  1.5T MRI, Ultrasound & Doppler  Cannulation & Gadolinium |  | **6** | **X** | **X** |
| 28+/- 3 days | **Visit 3**  1.5T MRI, Ultrasound & Doppler  Cannulation & Gadolinium | **X** | **7** | **X** | **X** |
| 28 +/- 3 days from Dose 1 Goserelin | GnRH agonist **Dose 2**  (Goserelin 3.6mg s/c) |  | **7A** | **X** | **X** |
| 28 +/- 3 days from Dose 2 Goserelin | GnRH agonist **Dose 3**  (Goserelin 3.6mg s/c) |  | **8** | **X** | **X** |
| Within 10 days of TAH | **Visit 4**  1.5T MRI, Ultrasound & Doppler  Cannulation & Gadolinium |  | **9** | **X** | **X** |
| 21-28 days from Dose 3 Goserelin | **Visit 5**  Hysterectomy  7T MRI of Uterus  Histo-morphology | **X** | **10** | **X** | **X** |

(Version 2 13th October 2009)

**In Addition -**

**Urine Sample (5mls) collected twice weekly from Visit 1**

**Daily Menstrual Recording Chart from Visit 1**

**Control – No Medication (n=10)**

| **Day of Treatment** | **Visits/Interventions** | **U&Es**  **FBC**  **LFTs** | **E2, P4,**  **LH, FSH**  **Time Points** | **Concomitant**  **Meds** | **Adverse Events** |
| --- | --- | --- | --- | --- | --- |
| Screening | Informed Consent  Inclusion & Exclusion Criteria  Medical & Menstrual History  Physical Exam & Vital Signs  Height & Weight  Urinalysis & Pregnancy Test  Ultrasound  Doppler (if required) | **X** |  | **X** |  |
| Within  28 days  of Day 1 | **Visit 1**  1.5T MRI, Ultrasound & Doppler (if required)  Cannulation & Gadolinium |  | **1** | **X** | **X** |
|  | **Randomisation** |  |  |  |  |
| 1  (Days 1 to 5 of cycle) | No Medication |  | **2** | **X** | **X** |
| 4+/- 1 day |  |  | **3** | **X** | **X** |
| 7+/- 1 day |  |  | **4** | **X** | **X** |
| 11+/- 1 day |  |  | **5** | **X** | **X** |
| 14+/-3 days | **Visit 2**  1.5T MRI, Ultrasound & Doppler  Cannulation & Gadolinium |  | **6** | **X** | **X** |
| 28+/-3 days from Visit 2 | **Visit 3**  1.5T MRI, Ultrasound & Doppler  Cannulation & Gadolinium | **X** | **7** | **X** | **X** |
| 28+/- 3 days from Visit 3 |  |  | **8** | **X** | **X** |
| Within 10 days of TAH | **Visit 4**  1.5T MRI, Ultrasound & Doppler  Cannulation & Gadolinium |  | **9** | **X** | **X** |
| 21-28 days from Visit 3 | **Visit 5**  Hysterectomy  7T MRI of Uterus  Histo-morphology | **X** | **10** | **X** | **X** |

(Version 2 13th October 2009)

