**Main Study:**

This will be an open investigational study. This study will be conducted in up to 30 women with uterine fibroids scheduled for hysterectomy. Patients will be allocated to 3 treatment groups (randomised). The randomisation scheme will be drawn up by an independent statistician, and the allocated treatment codes will be put into sealed consecutively numbered opaque envelopes. When a patient is randomised into the study, she will receive the treatment indicated in the next available envelope.

For approximately 12 weeks (Groups 1 and 3) and approximately 13 weeks (Group 2) prior to surgery (hysterectomy) the participants will receive one of 3 possible treatment options:

Group 1 n=10: a monthly sub-cutaneous injection of a GnRH agonist [Goserlin 3.6mg] (total of 3 injections) commencing from day 1-5 of menstrual cycle

Group 2 n=10: a GnRH antagonist [sub-cutaneous injection of Cetrorelix 3mg] given on 3 occasions (Day 1, 4 & 7 +/- 1 day) commencing day 1 to 5 of the menstrual cycle with a GnRH agonist (Goserelin 3.6mgs) thereafter monthly for 3 months, commencing day 7+/- 1 day.

Group 3 n =10: A control group of women with fibroids (no medication). Day 1 of the study will be a specified day between day 1 to 5 of their menstrual cycle.

NB – Monthly is defined by 28 days +/-3 days.

The hysterectomy will be performed 21-28 days from the last dose of GnRH agonist. The GnRH agonists can be given 28+/- 3 days apart. The GnRH analogue, Goserelin 3.6mg subcutaneous, and the 2nd and 3rd doses of cetrorelix 3mg subcutaneous, can be administered in the patients’ own homes if more convenient. However, dose one of cetrorelix must be given in the hospital with the patient observed for 30minutes after the drug is administered.

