**3.1.2 Measurements:**

Comparisons will be made between the following imaging modalities:

1. Sonographic assessment, colour Doppler imaging.
2. 1.5T MR imaging, including structural, dynamic contrast and magnetization transfer imaging.
3. Ex-vivo imaging with 7T MR scanner correlated with uterine histo-morphology.

For imaging exercises there will be one record per patient for each measurement at each time-point. The largest fibroid will be selected and total uterine volume measured.

It is not possible to have patients “blinded” to treatment option. It will be possible for the statistician, pathologists, radiologists, technicians and non clinical staff to be “blinded” to the treatment allocation, to the results of previous time-points, and to the results of other measures at the same time-point.

Following successful screening procedures all the participants will have a further 5 visits to the RIE.

On each of the visits 1 to 4 every participant will have a MRI, Ultrasound and Doppler. If Visit 1 falls within 28days of screening then the screening scan will remain valid. If this is anticipated then Dopplers will be carried out at screening.

Visit 1 will be carried out prior to randomisation (Within 28 days of Day 1)

Visit 2 at 14 days+/- 3 days following commencement of treatment

Visit 3 at 28 days+/- 3 days following commencement of treatment

Visit 4 Within 10 days prior to scheduled hysterectomy

Visit 5 Day of Hysterectomy and Ex-vivo imaging with 7T MR scanner of uterus

Blood samples will be taken on 3 occasions - at Screening, Day 28+/- 3 days (Visit 3)and on the day of Hysterectomy (Visit 5) to assess Urea and Electrolytes (U&E's), Full Blood Count (FBC), and Liver Function Tests (LFT's). These blood samples will be taken on scheduled study visits to the hospital.

A 10ml blood sample will be obtained on 11 occasions (Group 2) and 10 occasions (Groups 1 & 3) to obtain an estimate of Oestradiol (E), Progesterone(P), Luteinising Hormone (LH) and Follicle Stimulating Hormone (FSH). A small aliquot of blood will be stored in the freezer in reserve in case of any laboratory processing difficulties.

Some of these blood samples will be taken at the RIE when they coincide with Scheduled Study Visits. The participants will be given the option to have the rest of the blood samples taken in their own home if this is more convenient to them.

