# **STUDY ASSESSMENTS**

## **7.1 SAFETY ASSESSMENTS**

There are safety assessments for -

Pilot Group A at Screening, Day 28+/- 3 days and on day of hysterectomy.

Pilot Group B at Screening and on day of hysterectomy.

Pilot Group C at Screening and on day of hysterectomy.

Groups 1 to 3 at Screening, Day 28+/- 3 days and on day of hysterectomy.

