##### Clinical MR imaging will be performed. Patients will be examined on four occasions:

##### (1) before commencing GnRH agonist, GnRH antagonist therapy (visit 1);

##### (2) after 14 days+/- 3 days (visit 2);

##### (3) after 28 days +/- 3 days (visit 3);

##### (4) within 10 days prior to hysterectomy(visit 4)

Pre- and post GnRH agonist / GnRH antagonist treatment and control subjects will undergo breath-hold fast-spin-echo T2-weighted imaging acquired in planes oblique to the uterus, magnetization transfer, contrast-enhanced T1-volume scans and dynamic contrast imaging using a phased array torso coil on MR scanner.

Dynamic contrast imaging will use T1-weighted SPGR scans acquired at a number of time points after injection of gadolinium, e.g.  = 0, 30, 60, 90, 120 180, 240 and 300 seconds (Have practical limits in that patients usually become restless after about 30-40 minutes in MRI). Development work will be required to determine the optimum number and temporal resolution for this imaging to allow analysis of fibroid perfusion and permeability. Subjects will be carefully positioned so that the scan locations are as close as possible between pre- and post-treatment examinations. The use of image registration methods, such as FLIRT (www.fmrib.ox.ac.uk/fsl), to allow further fine alignment of imaging data will be investigated.

Uterus and enhancing and non-enhancing fibroid volumes pre- and post treatment will be determined from the T2- and T1-weighted structural scans using ANALYZE (Mayo Foundation, Rochester, MN, USA). Reduction in uterus and fibroid volumes will be determined as 100  (Volpre – Volpost)/Volpre.

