**7.2.5 Blood Sampling**

Pilot Group A

Blood samples will be taken on 3 occasions -

At Screening, Day 28+/- 3 days (to assess Urea and Electrolytes (U&E's), Full Blood Count (FBC), and Liver Function Tests (LFT's). and on the day of Hysterectomy (Visit 3) to assess as per previous visits plus Oestradiol (E), Progesterone(P), Luteinising Hormone (LH) and Follicle Stimulating Hormone (FSH)

Pilot Group B

Blood samples will be taken on 2 occasions -

At Screening (to assess Urea and Electrolytes (U&E's), Full Blood Count (FBC), and Liver Function Tests (LFT's) and on the day of Hysterectomy (Visit 2) to assess as per previous visits plus Oestradiol (E), Progesterone(P), Luteinising Hormone (LH) and Follicle Stimulating Hormone (FSH)

Pilot Group C

Blood samples will be taken on 2 occasions -

At Screening (to assess Urea and Electrolytes (U&E's), Full Blood Count (FBC), and Liver Function Tests (LFT's) and on the day of Hysterectomy (Visit 2) to assess as per previous visits plus Oestradiol (E), Progesterone(P), Luteinising Hormone (LH) and Follicle Stimulating Hormone (FSH)

Main Study

A 10ml blood sample will be obtained on 11 occasions (Group 2) and 10 occasions (Groups 1 & 3) to obtain an estimate of Oestradiol (E), Progesterone(P), Luteinising Hormone (LH) and Follicle Stimulating Hormone (FSH). Urea and Electrolytes (U&E's), Full Blood Count (FBC), and Liver Function Tests (LFT's) will be checked at screening, Day 28+/- 3 days (Visit 3) and on the day of Hysterectomy (Visit 5).

- - 1. **Urine Collection**

Main Study only

5mls urine samples collected twice weekly to measure sex steroid hormone metabolites. Up to 30 samples in total. Instructions will be given to participants. Patient is asked at each point of contact if collection is being completed and if more sample bottles are required. A small drop if glycerol is put into the sample bottles to help with the freezing process. This has no effect on the analysis of the sample.

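### The Appendix 4 control table puts Visit 3 at about Day 42 instead of Day 28, and hysterectomy at about 9–10 weeks instead of about 12

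*Protocol*

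**What the plan says.** For the main study, the body of the Protocol is consistent.

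- Section 3.1.2 (Measurements): "Visit 3 at 28 days+/- 3 days following commencement of treatment".
- Section 7.1 (Safety Assessments) names the control arm with the others: "Groups 1 to 3 at Screening, Day 28+/- 3 days and on day of hysterectomy".
- Section 7.2.3 (MR imaging) gives the same time for the third scan, and section 7.2.5 (Blood Sampling) gives it for the Visit 3 bloods.
- Section 3.1 (Main Study) sets the overall period: "For approximately 12 weeks (Groups 1 and 3) and approximately 13 weeks (Group 2) prior to surgery (hysterectomy").

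In Appendix 4, the Group 1 and Group 2 tables also place Visit 3 at 28±3 days from the start. Both count hysterectomy 21–28 days from the third goserelin dose.

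The control table uses other anchors. Visit 2 is at Day 14±3, Visit 3 is "28+/-3 days from Visit 2", hormone time point 8 is "28+/- 3 days from Visit 3", and hysterectomy (Visit 5) is "21-28 days from Visit 3". Visit 4, the pre-hysterectomy scan, is within 10 days before surgery in all three arms.

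**The concern.** The control table chains Visit 3 to Visit 2 instead of Day 1, and chains surgery to Visit 3 instead of to the control counterpart of the third goserelin dose. It therefore disagrees with the body text on two dates. It also disagrees with itself: time point 8 is listed before surgery, but its interval from Visit 3 is mostly longer than the interval from Visit 3 to surgery.

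Sections 3.1 and 7.2 send readers to Appendix 4 for the schedule. The section 3.1 rule for timing surgery counts from the last agonist dose, which controls never receive, so the faulty cell is the only day-count rule for control surgery. Three things are at stake if it is followed:

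- **Day 28 comparison.** Serial imaging at 14 and 28 days is how the Protocol studies the dynamics of response and the role of hypoestrogenism. A control scan at about Day 42 has no treated scan at a matching time. The Day 28 safety bloods, which include the renal check after repeated gadolinium (section 12.8.1), are delayed with it.
- **Time point 8.** Sections 3.1.2 and 7.2.5 require 10 hormone samples in Group 3. In the table's own order, the eighth can rarely be taken before surgery.
- **Primary comparison.** Section 9.2 compares pre-hysterectomy uterine volume between treated and control groups. The control scan would be taken after a shorter interval.

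**Working it through.** All times are elapsed days from Day 1, found by adding the intervals in each Appendix 4 table. Brackets give the limits when every window is at its extreme.

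**The Protocol's own figures**

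- Group 1: surgery = 28 + 28 + (21 to 28) = 77–84 days, or 11–12 weeks (limits 25+25+21 = 71 to 31+31+28 = 90). This agrees with the stated 12 weeks or so.
- Group 2: goserelin starts on Day 7±1, which is 6 (5–7) elapsed days. Surgery = 6 + 28 + 28 + (21 to 28) = 83–90 days (76–97). This is about 12–13 weeks, in line with the stated 13 or so.

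**Control table as written**

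| Event | Sum | Nominal day | Limits |
|---|---|---|---|
| Visit 2 | 14 | 14 | 11–17 |
| Visit 3 | 14 + 28 | 42 | 36–48 |
| Time point 8 | 14 + 28 + 28 | 70 | 61–79 |
| Surgery | 14 + 28 + (21 to 28) | 63–70 | 57–76 |

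Surgery at 63–70 days is 9–10 weeks, so the 12-week figure does not reproduce for controls.

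**Visit 3.** Control 36–48 against 25–31 in the treated arms. The nominal gap is 42 − 28 = 14 days and the smallest is 36 − 31 = 5 days. No choice of days within the windows reconciles them.

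**Time point 8 against surgery.** Both count from Visit 3: time point 8 at 25–31 days (7 values), surgery at 21–28 days (8 values), so 7 × 8 = 56 pairs.

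- Time point 8 after surgery: 46
- Same day: 4
- Before surgery, by 1–3 days: 6

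**Surgery and the final scan.** The midpoints of the surgery windows are 66.5 (control), 80.5 (Group 1) and 86.5 (Group 2). Control surgery is therefore 14 days before Group 1's and 20 days before Group 2's. About 6 of those 20 days are Group 2's intended longer regimen. Visit 4 has the same window before surgery in every arm, so the nominal gaps carry over to the scan. Of the 7 × 7 × 8 = 392 control combinations, 56 (14%) reach Group 1's earliest surgery day, 71.

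**Effect on the primary contrast.** The Protocol gives no figure for untreated change over two weeks. Assuming 1, 4 or 8 cm³ per week, the shift is 2 × 1 = 2, 2 × 4 = 8 or 2 × 8 = 16 cm³. Against the 160 cm³ difference in section 9.1, that is about 1%, 5% or 10%.

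**Correcting one cell or both**

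- Visit 3 cell only: surgery = 28 + (21 to 28) = 49–56 days (46–59), midpoint 52.5. That is 28 days before Group 1, worse than now.
- Both cells: Visit 3 at 28 (25–31), time point 8 at 56 (50–62), surgery at 77–84 (71–90). These are Group 1's windows.

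**The case against.** The strongest reply is that the body text already governs. Four sections give one time for Visit 3, section 7.1 names the control arm, and section 7.2 describes Appendix 4 as summaries. Harm follows only if staff book from the table, and the impossible order of time point 8 and surgery might alert them. That is fair, and it limits the severity. It does not settle surgery, because the body offers controls only an approximate number of weeks.

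Further points, and what stands of each:

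- **The treated-arm tables set no surgery date for controls.** Correct. On surgery the direct conflict is with section 3.1; the treated-arm tables contradict the control table directly on Visit 3.
- **The 14% describes surgery day, not the scan.** Correct. Taking the scan 1–10 days before surgery, control scans fall on Days 47–75 and Group 1 scans on Days 61–89; 2,121 of 3,920 control combinations (54%) reach Day 61. The scan windows overlap more than the surgery windows, but the nominal 14-day gap remains. All these counts weight days equally and are not probabilities.
- **The growth rates are assumed and the study is hypothesis-generating.** Both true. Changes over time are exploratory under section 9.2. The projected shift in the primary contrast is small and should not be pressed.
- **Day counting.** Reading Day 14 as 13 elapsed days moves control surgery to 62–69 and turns 56 of 392 into 35 of 392. Section 3.1.2 counts from the start of treatment, which supports 14; nothing reverses either way.
- **Other remedies exist.** Setting surgery about 12 weeks from Day 1 would also remove the conflict with section 3.1. Anchoring to time point 8 is preferable because it gives a day window identical to Group 1's.

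**Conclusion.** The contradiction is real and should be fixed. As written, the table puts control Visit 3 at Day 42 (36–48) against Day 28 (25–31) everywhere else, and control surgery at 9–10 weeks against about 12. Time point 8 falls on or after surgery in 50 of 56 combinations.

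These sums rest only on the Protocol's intervals. The consequences depend on staff scheduling from the table. In that case the main losses are the Day 28 control scan and time point 8, while the 14-day shift in the final scan probably moves the primary volume contrast little. That last judgement rests on the assumed 1–8 cm³ per week, for which the Protocol gives no source. The error is in an operative schedule, not in background text, but it does not undermine the design.

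**What to change.** Change two cells of the control table, in the same amendment:

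1. Visit 3: 28±3 days from Day 1.
2. Hysterectomy (Visit 5): 21–28 days from time point 8.

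Leave time point 8 at 28±3 days from Visit 3, and Visit 4 within 10 days before surgery. Do not correct the Visit 3 cell alone. Group 2's extra week stays as intended.

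In the report, give the actual days from Day 1 to Visit 4 by arm, descriptively, so that any controls already booked from the table can be seen.

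The cost is two table cells and one descriptive line. Section 14.1 still requires the amendment to go to the ethics committee, the regulatory authority and local R&D, so there is some administrative work, but no change to design, sample size or analysis.
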